### Primary outcome measures

#### Perception of fatigue

The symptoms of fatigue attributed to work-related physical, organizational, and psychosocial demands and stress will be evaluated using the Need for Recovery Scale (Br-NFR) [30–32]. This Likert-type scale has 11 questions with 4 possible responses (0 = never; 1 = sometimes; 2 = often; and 3 = always). The answer “always” indicates an unfavorable situation and receives 3 points, except for item 4, which has a reversed score. The total score is obtained by adding all of the scores and converting them into a scale ranging from 0 (lowest) to 100 (maximum) by means of a simple rule of three [32]. In this case, the higher the score is, the greater the number of symptoms and the greater the need for recovery.

#### Muscular fatigue

Muscular fatigue will be evaluated using the 1RM test, which is the maximum amount of weight that can be lifted one time while performing a standardized exercise. The test will be completed when the individual 1RM reference value is found. The one-repetition maximum will be tested in the following muscle groups: biceps, triceps, deltoid, quadriceps femoris, hamstrings, and triceps surae, using an appropriate load for the individual’s fitness level.

### Secondary outcome measures

#### Musculoskeletal symptoms

The presence of musculoskeletal symptoms (pain, tingling, or numbness) will be assessed using the Nordic Musculoskeletal Questionnaire (NMQ) [33]. The respondents will answer simple yes/no questions related to musculoskeletal symptoms in the last 12 months and/or in the past 7 days, the occurrence of functional disability, and the need to seek assistance from health professionals due to the symptoms. Pain intensity will be evaluated using the Pain Numeric Rating Scale [34], an 11-point scale in which 0 means “no pain” and 10 means “the worst possible pain.”

#### Level of physical activity

The Baecke Physical Activity Questionnaire [35] will be used to assess the level of habitual physical activity (HPA) of the participants. It is a reminder tool, consisting of 16 questions covering three HPA scores for the previous 12 months: physical activity at work, sport during leisure time and other physical activities during leisure and locomotion. The score obtained at baseline will be used to classify individuals as sedentary or active, and the follow-ups will show any changes in physical activity levels over the intervention period.

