### Supervision and training schedule

Interventions will take place over a period of 4 months, beginning in August 2016. The outcomes will be assessed at baseline, and there will be a follow-up at the end of the intervention. Both groups of participants will train for 20 min, 3 times a week on alternate days. All interventions will be carried out during working hours at the workplace, totaling 1 h per week. All exercise protocols developed for this study are shown in Appendix I.

Ten experts will be involved in the research and will receive 12 h of training on the protocol and objectives of the study, regardless of their role (assessors, instructors, or lecturers). The researcher will supervise the training sessions at the workplace. Heart rate and blood pressure will be measured before every session. If any significant change that could hinder training is identified in any vital signs, the participant will be sent to the company’s outpatient clinic for assessment.

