### Outcome measures

The primary outcome measures will be perception of fatigue and the secondary outcome measures will be musculoskeletal complaints and pain, quality of life, level of physical activity, physical condition, perceived exposure to risk factors, and productivity. The data collection instruments for these outcomes are described below. All outcomes will be evaluated at baseline and after 4 months (at the end program).

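### The 12-month Baecke recall is too long to show change over a 4-month programme as the protocol claims; the 12-month NMQ items share the weakness, but the 7-day item and pain rating do not

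*Protocol article*

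**What the plan says.** All references are to the protocol article.

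- **Level of physical activity:** the Baecke questionnaire is described as "covering three HPA scores for the previous 12 months". The baseline score classifies workers as sedentary or active. For later assessments the text says that "the follow-ups will show any changes in physical activity levels over the intervention period".
- **Musculoskeletal symptoms:** the NMQ asks "simple yes/no questions related to musculoskeletal symptoms in the last 12 months and/or in the past 7 days". In addition, "Pain intensity will be evaluated using the Pain Numeric Rating Scale", scored 0 to 10, with no 12-month window stated.
- **Supervision and training schedule:** "Interventions will take place over a period of 4 months", with one follow-up at the end.
- **Outcome measures:** physical activity and musculoskeletal complaints and pain are secondary outcomes. Every outcome is assessed at baseline and again at 4 months, when the programme ends.
- **Productivity:** the single question looks back 3 months, which fits inside the programme.

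**The concern.** A recall measure can show change over a period only to the extent that its window falls in that period. Here the follow-up window is three times as long as the programme, so most of what a worker is asked to recall at month 4 happened before the programme began. The Baecke follow-up score therefore mixes the two periods, while the text presents it as a measure of change during the programme.

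What is at stake is how a null result is read. If the arms do not differ on the Baecke score at 4 months, the quoted sentence invites the conclusion that activity did not change differently between them. The instrument as described gives little basis for that conclusion.

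The 12-month NMQ items have a related limit. A worker with symptoms in the 8 months before baseline, answering accurately, must still say yes at month 4 even if symptom-free throughout the programme.

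**Working it through.** **Inputs from the article.** Baecke recall 12 months; NMQ recall 12 months and 7 days; productivity recall 3 months; programme 4 months; single follow-up at 4 months. For the illustration in step 4: 86 per group after allowing for 15% loss, α = 0.05, power 80% (Sample size section).

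**1. Share of the follow-up window before the programme.**
(12 − 4)/12 = 8/12 = 67% before; 4/12 = 33% during.
The same calculation gives 0% before for the NMQ 7-day item and for the 3-month productivity question.

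**2. What the change score then compares.** Number months from the start of the programme. The baseline window is the 12 months before month 0. The follow-up window is the last 8 of those months plus months 1 to 4. If the score is an equally weighted average of the 12 months (assumption), the shared 8 months cancel:

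follow-up − baseline = (4/12) × (mean of the 4 programme months − mean of the earliest 4 months of the baseline window).

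So the recorded change is one third of a difference, and the comparison period is the stretch furthest before the programme, not the one just before it.

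**3. Between-arm contrast.** Randomised arms have the same expected pre-programme level. A true between-arm difference Δ during the programme therefore appears as (8/12) × 0 + (4/12) × Δ = Δ/3.

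**4. Illustration of the loss of information.** The article gives no standard deviation for the Baecke score, so standardised effects are assumed. Evaluable workers per arm: 86 × 0.85 = 73.1, taken as 73. The effect detectable with 80% power, two-sided, is (1.960 + 0.842) × √(2/73) = 0.464. Power is Φ(d × √(73/2) − 1.960), with √(73/2) = 6.04, the SD unchanged and no allowance for clustering (assumptions). The weight given to the programme months is varied because respondents may not weight months equally.

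| Weight on programme months | Recorded d if true d = 0.464 | Power | Recorded d if true d = 0.8 | Power |
|---|---|---|---|---|
| 1 (no dilution) | 0.464 | 80% | 0.800 | 99.8% |
| 2/3 | 0.309 | 46% | 0.533 | 90% |
| 1/2 | 0.232 | 29% | 0.400 | 68% |
| 1/3 (equal weights) | 0.155 | 15% | 0.267 | 36% |

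With equal weights the sample needed for the same power rises by 1/(1/3)² = 9.

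**5. NMQ 12-month items.** The limit is logical and needs no model. An accurate yes that rests on any of the 8 pre-programme months cannot become no at month 4. A change from yes to no is possible only for a worker whose symptoms all fell in the earliest 4 months of the baseline window. No size is given, because the article states no symptom rates.

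**The case against.** Much can be said on the other side.

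- **A reader might infer that two secondary outcomes cannot show change at all.** The article does not support that. The NMQ has a 7-day item lying wholly within the programme at follow-up, and a pain rating sits beside it, so the musculoskeletal outcome already has usable measures. For the Baecke score the effect is attenuated, not removed, and because both arms share the overlap the bias is towards no difference. This stands, and it limits the point to the Baecke score and the 12-month NMQ items.
- **A reader might infer that the article makes the same claim for the NMQ.** It does not: the sentence about change over the intervention period concerns physical activity only.
- **A reader might see in the two NMQ windows a licence to choose one after seeing the data.** In context the wording describes what respondents are asked and sets no reporting rule. Which item is analysed may be fixed in a full protocol or analysis plan that is not shown, so no charge of selective reporting follows.
- **The 7-day item is not necessarily the more powerful one.** It will usually pick up fewer symptomatic workers. This is correct. The reason to prefer it is that it describes the right period, not that it guarantees power.
- **The power figures depend on assumptions.** They do. The SD may not stay the same, and baseline adjustment could remove some of the noise from the shared months. Clustering by sector would lower every figure. The table shows direction and rough size only.

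None of this rescues the quoted Baecke sentence, which ascribes to the follow-up a property that the described window does not give it.

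**Conclusion.** The point holds in a limited form. The mismatch between a 12-month Baecke recall and a single 4-month follow-up is in the article's own figures: 67% of the follow-up window precedes the programme and is shared with baseline. If the score acts as a 12-month average, a between-arm change is recorded at about one third of its size; heavier weighting of recent months would lessen this. A null Baecke result would therefore say little about activity during the programme, contrary to the sentence in the physical activity section. The 12-month NMQ items are insensitive for the same reason; the 7-day item and the pain rating are not. The consequence is confined to secondary outcomes and does not reach the primary fatigue analysis.

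**What to change.** 1. **NMQ:** name the 7-day item and the pain numeric rating as the symptom outcomes for between-arm change at 4 months, and keep the 12-month items as baseline descriptors. Both measures are already planned, so this adds no data collection.
2. **Baecke:** replace the claim about change over the intervention period with a statement that the 12-month score is diluted for change over 4 months and that a null result is not evidence of no change. This is an edit to one sentence.
3. **Optional:** shorten the Baecke recall only if the same shorter period is used at baseline and at follow-up, and report the departure from the 12-month form. Changing it at follow-up alone would compare unlike windows. The article gives the trial status as ongoing, with interventions from August 2016; if baseline data have been collected, a matching period may no longer be obtainable and item 2 is the workable choice.

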#### Perceived risk

In this study, we will use the Job Factor Questionnaire to evaluate the workers’ perception of risk factors associated with the development of musculoskeletal complaints [36]. This instrument presents a descriptive list of 15 risk factors that are rated on a scale of 0 to 10 according to their contribution to the emergence of work-related musculoskeletal symptoms, with 0 indicating “no problem” and 10 indicating the “largest possible problem.”

#### Physical fitness assessment

Postural assessment - static assessment to identify postural changes with asymmetry that may affect training. This assessment will be carried out by direct observation and recorded on a specific form.Vital signs - heart rate, respiratory rate, lung auscultation, blood pressure, and oxygen saturation. These signs will be assessed using a heart monitor (POLAR - RS800CX), a fingertip pulse oximeter, a stethoscope, and a sphygmomanometer. The aim is to monitor the individual before, during, and after exercise.Body Mass Index (BMI) - a widely used parameter to estimate an individual’s health according to their weight and height. The World Health Organization (WHO) uses this index as an indicator of obesity levels in different countries. It is calculated by dividing the weight (kg) by the height squared (meters).Waist-Hip Ratio (WHR) and Waist Circumference - WHR is an excellent way to identify the existence of increased risk for cardiovascular disease. Scientific studies have shown that a high concentration of abdominal fat (near the heart), without even considering the degree of obesity, is a risk factor for the development of heart disease [37]. The following equation will be used to measure WHR: waist measurement divided by hip measurement (W ÷ H). The higher the values are, the higher the risk. Results greater than or equal to 0.8 for women and 1.0 for men indicate a high risk for cardiovascular disease. Waist circumference is a measure that helps identify the people most likely to suffer from cardiovascular diseases [38] and it is as important as the BMI. A circumference greater than or equal to 94 cm in men and 80 cm in women is an indicator of a 3.25 times higher risk of developing heart disease [38]. A tape measure will be used to measure waist circumferences.Body Fat Percentage - assessed with a body fat caliper commonly used in epidemiological research, outpatient clinics, doctor’s practices, and gyms. This apparatus features rulers that measure the fat in the skinfolds at different sites (triceps, biceps, pectoralis, subscapularis, midaxillary, suprailiac, abdomen, thigh, and calf). With these measurements, the professional can make a precise assessment of body composition and monitor the patient accordingly.One-Repetition Maximum (1RM) - this test evaluates muscle strength. It measures the maximum amount of weight that an individual can lift in a single repetition. The 1RM will be tested in the following muscle groups: biceps, triceps, deltoid, quadriceps femoris, hamstrings, and triceps surae using an appropriate load for the individual’s fitness level. Dumbbells, weight plates, and other conventional weights will be used for this measurement [26].Somatotype Rating - this assessment will identify the workers’ body type or physical classification. The terms endomorph (fat), mesomorph (muscular), and ectomorph (thin) will be used to describe the workers’ somatotype according to their weight, height, and body fat percentage at baseline [26].Neck Circumference (NC). This measure is indicative of the level of obesity. A very large neck circumference may be related to increased risk of heart disease and metabolic disorders. A neck circumference ≥ 37 cm for men and ≥ 34 cm for women is equivalent to a BMI ≥ 25 kg/m^2^. A neck circumference ≥ 39.5 cm for men and ≥ 36.5 for women is equivalent to a BMI ≥ 30 kg/m^2^. A neck circumference of up to 37 cm in men and up to 34 cm in women indicates a normal BMI [39]

#### Productivity

The workers’ will answer a single question related to productivity at work during the follow up. This question is one of the items on the WHO Health and Work Performance Questionnaire (HPQ) [40] and asks the respondent to assign a score (0–10) to their work productivity over the previous 3 months.

#### Sample size

The sample size calculation is based on the difference detected in the Need for Recovery Scale (Br-NFR) [30, 31], that is, 20%. This difference was detected in the analysis of the average need for recovery observed over 7 working days and assessed at the beginning and the end of the shifts of 123 workers. Considering α = 0.05, a statistical power of 80%, and a sample loss of up to 15%, the sample size required per group is 86 workers (172 workers in total).

#### Statistical analysis

The data will be monitored by a committee not involved with data collection in order to avoid conflict of interest. A researcher will receive the encoded data and perform the statistical analysis. All data will be entered into the database twice, and the coding will be blinded. Descriptive statistics (frequencies, means, standard deviation, standard error, confidence interval) will be used to analyze the sociodemographic characteristics of the participants. The Shapiro-Wilk test will be used to assess the normality of the data. The chi-square test will be used to evaluate assessor blinding through a comparison between randomization codes and the assessors’ guesses. The difference between the groups and their respective confidence intervals will be calculated using a mixed linear model. The significance level will be 5%. The statistical program SPSS Statistics 24.0 will be used for all analyses, which will be performed on an intention-to-treat basis.

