**Methods/Design:**

This is a cluster randomized controlled trial with two arms and is assessor blinded. A total of 352 workers of both sexes, aged 18–65 years, from a medium-sized dairy plant were enrolled in this study. Participants will be recruited from 13 production sectors according to the eligibility criteria and will be randomized by clusters to either the Progressive Resistance Exercise (PRE) intervention group or the Compensatory Workplace Exercise (CWE) comparative group. A resistance exercise program will be implemented for both groups. The groups will receive instructions on self-management, breaks, adjustments to workstations, and the benefits of physical exercise. The PRE group will perform resistance exercises with gradual loads in an exercise room, and the CWE group will perform exercise at their workstations using elastic bands. The exercise sessions will be held 3 times a week for 20 min. The primary outcome measures will be symptoms of physical and mental fatigue, and muscular fatigue based on a one-repetition maximum (1RM). The secondary outcome measures will be level of physical activity, musculoskeletal symptoms, physical condition, perceived exposure, and productivity. The workers will be assessed at baseline and after a 4-month program. A linear mixed model will be applied on an intention-to-treat basis.

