### Eligibility criteria

The dairy plant has 600 employees among its administrative and production sectors. The study will focus on the production sector, which enrolled 352 workers. The inclusion criteria will be as follows: permanent employment status, fixed work shifts, agreement to participate, and signing the informed consent form. The exclusion criteria will be temporary employment status, vacation, or sick leave to ensure group comparability, the feasibility of the interventions, and blinding.

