### Randomization

Prior to clustering according to exposure level, 13 of the plant’s production sectors will be included in the study: Boilers, Processing, Receiving/Cooling/Standardization, Milk, Butter, Cheese, Milk Caramel, Yoghurt, UHT Plant, Milk Powder, Stock, and Warehouse. Allocation will be performed on Research Randomizer (https://www.randomizer.org/) by a researcher not involved with the data collection.

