### Blinding

Due to the nature of the intervention, it is not possible to blind the workers and physical therapists who carry out the interventions. However, the researchers who will conduct the interviews and assessments will be blinded (double blinded). After the assessment, the blinding will be tested by having the researchers guess the type of intervention the worker received: Progressive Resistance Exercise (PRE) intervention group or the Compensatory Workplace Exercise (CWE) and write it down.

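### The chi-square test of assessor blinding ignores cluster allocation, so its 5% error rate may be exceeded if guesses correlate within clusters

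*Protocol article*

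**What the plan says.** Four statements in the protocol article bear on this point.

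- **Unit of allocation.** The abstract says workers "will be randomized by clusters to either the Progressive Resistance Exercise (PRE) intervention group" or the comparative group. Study design also calls the trial cluster randomised.
- **Unit of the guess.** Under Blinding, "the blinding will be tested by having the researchers guess the type of intervention the worker received", so there is one guess per worker.
- **Test.** Statistical analysis: "The chi-square test will be used to evaluate assessor blinding through a comparison between randomization codes" and the guesses. The same section sets a 5% significance level and names no allowance for clustering in this test. The mixed linear model is named only for the difference between groups.
- **Clusters.** The abstract says "Participants will be recruited from 13 production sectors according to the eligibility criteria". Randomization says "Prior to clustering according to exposure level, 13 of the plant’s production sectors will be included in the study", then lists 12 names. The final number of randomised units is not given.

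**The concern.** A Pearson chi-square test of guess against arm takes its variance from independent binary observations. Here all workers of a randomised cluster have the same arm, and their guesses may resemble one another. An assessor who forms a view about a sector, right or wrong, may repeat it for many of its workers. The interview records each worker's current role, which could reveal the sector.

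If that happens, the difference in guesses between arms varies more by chance than the test allows, and the p-value is too small. The trial could then report that assessor blinding failed when the guesses carried no information on arm. This is the only check of assessor blinding in the document, and the primary outcomes include a one-repetition-maximum test carried out by assessors.

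**Working it through.** **Inputs from the protocol article**

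- Nominal level 5% (Statistical analysis).
- Sectors: 13 stated, 12 listed (Randomization). Both are used.
- Workers: 172 required (Sample size) and 352 in production (Eligibility criteria). These bracket the number of guesses.

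**Assumed, because the document does not give it**

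- Intracluster correlation ρ of the guesses: 0 to 0.10.
- Sectors are the randomised clusters, equal in size, split 6:6 or 6:7.
- Guesses are unrelated to arm and equally likely to name either arm.

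**Step 1: the plan's own figure.** With ρ = 0 the test has the stated size: 2[1 − Φ(1.96)] = 5.0%. Simulation (100,000 runs per cell) gives 4.9–5.5%.

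**Step 2: allow for clustering.** With m workers per sector, the variance of the difference in guess proportions is multiplied by

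DE = 1 + (m − 1)ρ

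and the true size of the unadjusted test is about

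2[1 − Φ(1.96 / √DE)].

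Worked case: 352 workers in 13 sectors give m = 352/13 = 27.1. At ρ = 0.05, DE = 1 + 26.1 × 0.05 = 2.30. Then 1.96/√2.30 = 1.29, and the size is 19.7%.

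**Step 3: results.** Each cell gives the formula value, then the simulated value (beta-binomial guesses, sector sizes as equal as possible).

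| ρ | 172 workers, 13 sectors | 172, 12 sectors | 352, 13 sectors | 352, 12 sectors |
|---|---|---|---|---|
| 0 | 5.0 / 5.0% | 5.0 / 5.5% | 5.0 / 5.0% | 5.0 / 4.9% |
| 0.01 | 6.4 / 6.6% | 6.6 / 7.3% | 8.1 / 8.2% | 8.4 / 8.1% |
| 0.02 | 7.9 / 8.2% | 8.2 / 8.9% | 11.2 / 11.4% | 11.7 / 11.6% |
| 0.05 | 12.3 / 12.4% | 12.9 / 14.0% | 19.7 / 19.9% | 20.7 / 20.4% |
| 0.10 | 18.9 / 19.1% | 19.9 / 21.1% | 30.2 / 30.7% | 31.7 / 31.9% |

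Unequal sectors raise the figures somewhat. With 352 workers, 13 sectors and ρ = 0.10, sizes ranging from 0.3 to 1.7 times the mean gave 34.2%. Whether there are 12 or 13 sectors matters little.

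**Step 4: check the remedies.**

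- A permutation test that re-randomises arm labels across sectors rejected in 4.8–5.1% of null simulations (4,000 runs per cell, ρ = 0.05 and 0.10). A 6:7 split of 13 sectors has 1,716 possible allocations and a 6:6 split of 12 has 924, enough for a 5% test.
- A percentile bootstrap that resamples the 6 sectors of one arm is not adequate. Its nominal 95% interval for that arm's proportion covered only 85–88% (ρ = 0.05 to 0.30).

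**The case against.** **The inflation needs ρ above zero, and nothing in the document shows that.** No correlation of guesses is given. The document does not say that one assessor sees a whole sector, or how guesses are formed. This stands. A reader might infer that the 5% level is certainly breached. The document supports only that it is breached if guesses correlate within clusters, and that the excess is small when the correlation is near 0.01.

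**Strong agreement within a sector may be real unblinding.** An assessor may learn whether a sector trains in the exercise room or at its workstations. Rejection is then correct, not a false positive. This is a fair reason not to rest the point on high correlations, so the range above stops at 0.10.

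**Little depends on the test.** No decision, sensitivity analysis or outcome estimate is tied to it, and no pass/fail rule is written. This also stands. A reader might infer that the treatment comparison is compromised. It is not: group differences come from the mixed linear model. Nor is assessor blinding the only blinding in the trial, since the analyst receives coded data. It is only the blinding that is tested.

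**An article may leave such detail to an analysis plan.** That would answer a missing detail. Here the article names a specific test, and that test as named does not match the design. An adjusted version may be intended, but nothing says so.

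**The randomised unit is unclear.** The Randomization section may mean that sectors are grouped by exposure level before allocation. Clusters would then be fewer and larger, and at the same ρ the inflation would be greater. This does not weaken the point, but the fix must refer to the units actually randomised.

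**Conclusion.** The point holds in a conditional form. The named test ignores the unit of allocation, and any positive within-cluster correlation of guesses pushes its error rate above 5%. Going from 172 to 352 workers, the rate is about 7% to 8% at a correlation of 0.01, 12–14% to about 20% at 0.05, and 19–21% to 30–32% at 0.10. These figures rest on an assumed correlation, on 12 or 13 equal sectors being the randomised clusters, and on guesses unrelated to arm.

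The error is mainly towards a false alarm about assessor blinding. It leaves the outcome estimates and their intervals untouched. This is a worthwhile, low-priority correction.

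**What to change.** In Statistical analysis, replace the chi-square test with one of the following:

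- a permutation test that reassigns arm labels across the clusters actually randomised, following the allocation scheme used (preferred); or
- a cluster-adjusted test of guess against arm with a small-sample correction.

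Also report the proportion of correct guesses in each arm with a small-sample cluster-level interval, for example a t interval computed from the cluster proportions. Do not use a percentile bootstrap of about 6 sectors per arm.

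State in Randomization what the randomised clusters are and how many there are, because the permutation depends on it. If sectors were merged into very few clusters, a 5% permutation test may be impossible. With 4 clusters split 2:2, for illustration, there are 6 allocations and the smallest two-sided p-value is 2/6 = 0.33. In that case report the estimates alone.

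The cost is slightly more analysis work and a wider interval. The only extra item needed is each worker's cluster, which allocation already requires.

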## Methods

### Study design, approval, and registration

This is a cluster randomized controlled trial (RCT) two-arm (parallel group) with double blinded (investigator and assessor). The study protocol was approved by the Institutional Research Ethics Committee (Approval Number: 454709) according to the Helsinki Declaration as revised in 2013. Previously registered at ClinicalTrials.gov under protocol number NCT02172053. This protocol was reported according to SPIRIT guidelines.

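### The plan does not say that the randomised cluster enters the mixed model, and a worker-only model that complies with the text could miss the 5% level by a wide margin

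*Protocol article*

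**What the plan says.** - **Design.** The section on study design states: "This is a cluster randomized controlled trial (RCT) two-arm (parallel group". The abstract adds: "Participants will be recruited from 13 production sectors according to the eligibility criteria and will be randomized by clusters".
- **Randomised unit.** The Randomization section opens with "Prior to clustering according to exposure level, 13 of the" and goes on to list the plant's production sectors. Thirteen are announced. Twelve names follow, counting the combined receiving, cooling and standardization entry as one. How exposure level turns sectors into clusters is not explained.
- **Analysis.** The Statistical analysis section says: "The difference between the groups and their respective confidence intervals will be calculated using a mixed linear model". The level is 5% and the analysis is by intention to treat. The abstract says no more. No fixed term, random term or degrees-of-freedom method appears, nor does the role of the baseline score.
- **Visits.** Under Outcome measures: "All outcomes will be evaluated at baseline and after 4 months (at the end program".
- **Size.** Under Eligibility criteria: "The study will focus on the production sector, which enrolled 352 workers". Under Sample size: "Considering α = 0.05, a statistical power of 80%, and a sample loss of up to 15" per cent lead to the conclusion that "the sample size required per group is 86 workers (172 workers in total". No ICC, design effect or number of clusters is given.

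**The concern.** In a cluster trial, the arm comparison must be judged against variation between clusters. A mixed model can do this, but only if the randomised unit is one of its random effects. With two visits per worker, there is another obvious reason to use a mixed model, namely repeated measures within worker. An analyst who fits only a worker random effect has followed the plan as written.

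The sample size section makes this more than an omitted detail. It is a positive statement about how the comparison was planned, and it treats workers as independent. Clustering therefore appears in neither of the two statistical sections. What is at stake is the 5% level that the plan states: a worker-only analysis would work with hundreds of degrees of freedom for a comparison that has about 11 (13 clusters minus 2), or fewer if sectors are merged.

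**Working it through.** **1. The plan's own sample size.** 73 / (1 − 0.15) = 85.9, so 86 per group and 172 in total. With n = 2(z₀.₉₇₅ + z₀.₈₀)² / d², 73 per group needs d² = 15.70 / 73 = 0.215, so d = 0.464. The stated 20% gives this only with a standard deviation (SD) of 43 points (20 / 0.464) if it means points, or 43% of the mean if it is relative. The documents give no SD. Pairs of proportions such as 35% v 15% also lead to 73 and then 86, but none is stated. So 86 can be matched only with an assumed input, and every match found uses a formula for individually randomised workers.

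**2. Cluster left out, follow-up scores compared.**

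Inputs from the article: 352 workers, 172 required, 15% loss, 13 sectors. Assumed: 6 v 7 allocation with sector as the cluster, and an ICC of 0.01 to 0.10. The figure of 299 is 352 × 0.85.

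Mean cluster size is m = N / 13, that is 27.1, 23.0 and 13.2 for 352, 299 and 172. The design effect is DE = 1 + (m − 1) × ICC. True type I error is 2[1 − Φ(1.96 / √DE)].

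| ICC | 352 workers | 299 workers | 172 workers |
|---|---|---|---|
| 0.01 | 8.1% | 7.6% | 6.4% |
| 0.02 | 11.2% | 10.2% | 7.9% |
| 0.05 | 19.7% | 17.6% | 12.3% |
| 0.10 | 30.2% | 27.3% | 18.9% |

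Example, 352 workers at ICC 0.10: DE = 1 + 26.08 × 0.10 = 3.61, √DE = 1.90, 1.96 / 1.90 = 1.03, giving 30.2%. A simulation with 13 unequal sectors and 299 workers gave 7.9%, 10.8%, 19.1% and 30.9%, slightly above the formula. A t-test on sector means in the same simulation held 4.4-4.7%.

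**3. Interval width.** The correct interval exceeds the worker-level one by √DE × t₁₁ / 1.96, where t₁₁ = 2.201 and 2.201 / 1.96 = 1.123. Over the ICC range the ratio is 1.26 to 2.13 with 352 workers and 1.19 to 1.67 with 172.

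**4. Both visits modelled, worker the only random factor.** This amounts to comparing changes, so sector differences that are constant over time cancel. With total variance 1 at each visit, assumed within-worker residual correlation 0.6, and ρ the correlation of sector effects between visits:

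- between-sector variance of change: 2 × ICC × (1 − ρ)
- within-sector variance of change: 2 × (1 − ICC) × 0.4

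At ICC 0.10 and ρ = 0.8 these are 0.04 and 0.72. The ICC of change is 0.04 / 0.76 = 0.053, DE = 2.37, and the error is 20%. At ρ = 0 they are 0.20 and 0.72, the ICC of change is 0.217, DE = 6.67, and the error is 45%. At ICC 0.01 the same steps give 6.5% and 12.6%. Simulation with 352 workers in unequal sectors gave 23-50% at ICC 0.10 and 7-14% at ICC 0.01. At ρ = 1 the between-sector term is zero and there is no inflation.

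**5. Cluster in the model, normal reference.** P(|t₁₁| > 1.96) = 7.6%, or 7.8% on 10 degrees of freedom (12 clusters). The correct interval is 12% or 14% wider.

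**6. Baseline score.** With an assumed correlation of 0.5 between visits, adjustment leaves 1 − 0.5² = 0.75 of the worker-level residual variance, against 1 for follow-up scores alone and 2(1 − 0.5) = 1 for change scores. This affects precision, not the validity of the interval.

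**The case against.** The strongest reply is that nothing in the article says the cluster is omitted. It pairs cluster randomisation with a mixed model, which is a standard way to handle clustering, and an article may leave random effects, degrees of freedom and covariates to a fuller document. This stands against one tempting inference: a reader might conclude that the planned model ignores sector. The documents do not show that. They show only that the stated plan permits it. The reply does not dispose of the point, because the sample size section is not silent: it sizes the trial with no allowance for clustering, which suggests an oversight and not mere abbreviation.

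Three further objections are right and limit the claim:

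- It would be too strong to say that any sector difference would be read as a treatment effect. In a two-visit model, stable differences cancel; only sector-specific change inflates the error.
- A reader might think that leaving out the baseline score also makes intervals too narrow. It does not; it costs precision and control of chance imbalance. A two-visit model already uses baseline as an outcome. The 25% reduction in step 6 concerns worker-level variance and need not carry over to the treatment effect when variation between sectors matters.
- At the low end the harm is small: 6.4% with 172 workers at ICC 0.01. The degrees-of-freedom issue alone is moderate.

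**Conclusion.** The point holds as a failure to fix the unit of inference. The article does not tie its mixed model to the randomised cluster, its sample size ignores clustering, and a worker-only model complies with the text.

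If the cluster were left out, type I error for a follow-up comparison would be about 8-30% with 299-352 workers and 6-19% with 172. For a change-score model the size depends also on the persistence of sector effects. If the cluster is included but a normal reference is used, the error is about 7.6%.

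The follow-up figures rest on an assumed ICC of 0.01 to 0.10 and on sector as the cluster, with 13 of them. The change-score figures add two assumed correlations. If sectors are merged by exposure level, there are fewer clusters and the problem is worse.

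**What to change.** 1. Reconcile the Randomization section, so that the randomised unit is defined and its number is fixed: 13 sectors announced, 12 named, and grouping by exposure level unexplained.
2. State that this unit is a random effect in the primary model, with worker nested within it if both visits are modelled.
3. Name a Satterthwaite or Kenward-Roger type method. Degrees of freedom are about the number of clusters minus 2, less one for each cluster-level covariate: about 11 with 13 clusters, and about 10 if a sector-mean baseline is added.
4. Support the result with a t-test on cluster-level summaries.
5. Separately, and for precision only, adjust for each worker's baseline score on the Need for Recovery Scale, which is already collected. Include terms for allocation strata only if strata are actually used; the article describes none.

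This changes wording only and needs no new data. The cost is wider confidence intervals, by the factors in step 3 of the working if the comparison would otherwise be made at worker level.
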